**Method/design:**

The Tapas-study is a three-arm multicenter prospective cohort study.

All patients with colon carcinoma, eligible for surgical treatment within the study period in four general teaching hospitals and one university hospital will be included. This design produces three cohorts: Conventional open surgery is the control exposure (cohort 1). Open surgery with ERAS recovery (cohort 2) and laparoscopic surgery with ERAS recovery (cohort 3) are the alternative exposures. Three separate time periods are used in order to prevent attrition bias.

Primary outcome parameters are the two main cost factors: direct medical costs (real cost price calculation) and the indirect non medical costs (friction method). Secondary outcome parameters are mortality, complications, surgical-oncological resection margins, hospital stay, readmission rates, time back to work/recovery, health status and quality of life.

Based on an estimated difference in direct medical costs (highest cost factor) of 38% between open and laparoscopic surgery (alfa = 0.01, beta = 0.05), a group size of 3×40 = 120 patients is calculated.

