#### Sample size calculation

We used an extensive table to calculate all direct medical costs including overhead and consultant costs for open and laparoscopic colon surgery for an average Dutch hospital. The main cost differences were due to the difference in operating time, use of (disposable) laparoscopic instruments and hospital stay. Based on our costs calculation, for each patient the difference in direct medical costs between laparoscopic colectomy en open colectomy is 2967 euro (38%). Considering approximately 9000 colon carcinoma operations performed annually in the Netherlands http://www.prismant.nl, the hypothetical direct costs of all 'open' colectomies performed are 38.7 million euro. The hypothetical direct costs of laparoscopically colectomies for the Netherlands are 65.3 million euro. Performing all colectomies in the Netherlands by a laparoscopic technique would result in 26.7 (= 38%) euro extra direct costs compared to performing all colectomies by the open technique.

Power calculation of the study

p1 (direct medical cost of laparoscopic colon surgery in the Netherlands) = 100 %

p2 (direct medical cost of open colon surgery in the Netherlands) = 62%

alfa = 0.01, beta = 0.05, f = 17.8

Based on differences of approximately 2000 euro found in literature form other countries, the number needed in each group would be n = 43. Therefore a more conservative trial size of 3 × 40 = 120 patients is taken into account.

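### The plan states a need of 43 per group for a 2000 euro difference, adopts 40 and calls it more conservative; the abstract bases the same 120 on a different effect

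*Protocol article*

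**What the plan says.** The Sample size calculation section works from the sponsor's own cost table, which puts laparoscopic colectomy 2967 euro, or 38%, above open colectomy. Under its power calculation it prints "p1 (direct medical cost of laparoscopic colon surgery in the Netherlands) = 100" per cent, "p2 (direct medical cost of open colon surgery in the Netherlands) = 62" per cent, and "alfa = 0.01, beta = 0.05, f = 17.8". It prints no formula, and no group size for these inputs.

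It then moves to a smaller effect: "Based on differences of approximately 2000 euro found in literature form other countries". For this it states that "the number needed in each group would be n = 43. Therefore a more conservative trial size of" 3 × 40 = 120 patients is adopted. The second sentence, joined to the first by a *therefore*, thus describes 40 per group as the more conservative size.

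The abstract (Method/design) gives the same total and the same alpha and beta, but a different starting point: "Based on an estimated difference in direct medical costs (highest cost factor) of 38% between open and laparoscopic surgery". It does not mention the 2000 euro difference.

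**The concern.** Two statements do not fit together.

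- **Direction.** A conservative sample size is at least as large as the calculated need. Here the need is given as 43 and the adopted size is 40, yet the text presents 40 as following from 43 and as the cautious choice.
- **Basis.** The abstract draws 120 from the 38% difference. The methods section attaches it to the 2000 euro sentence. A reader cannot tell which effect the trial was sized for.

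At stake is the accuracy of the stated error rates. A reader of the methods section would take beta = 0.05 to hold for a 2000 euro difference. On the plan's own numbers it does not.

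**Working it through.** **Inputs, all from the Sample size calculation section:** alpha 0.01; beta 0.05; f = 17.8; p1 = 1.00; p2 = 0.62; cost difference 2967 euro (38%); second scenario about 2000 euro with 43 per group; adopted size 40 per group.

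**1. The multiplier f.** (z₀.₉₉₅ + z₀.₉₅)² = (2.576 + 1.645)² = 17.8, which matches. So alpha is two-sided; one-sided would give 15.8.

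**2. The stated 43.** No formula is printed, so this step is an inference. The unpooled two-proportion formula is n = f × [p1(1 − p1) + p2(1 − p2)] / (p1 − p2)². With p1 = 1 it reduces to n = f × p2 / (1 − p2).

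- Laparoscopic cost implied by 2967 euro = 38%: 2967 / 0.38 = 7808 euro. Open cost: 7808 − 2967 = 4841 euro.
- With a 2000 euro difference on that open cost: p2 = 4841 / 6841 = 0.708.
- n = 17.8 × 4841 / 2000 = 43.1, which reproduces the stated 43.

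The base cost of 4841 euro is an assumption, since the article does not say which base it used. Other bases derivable from the text give 38.3 (open 4300 euro, from 38.7 million / 9000), 46.8 (laparoscopic 7256 euro, from 65.3 million / 9000) and 51.7 (laparoscopic 7808 euro).

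**3. Power at 40 for the 2000 euro scenario.** This step needs only the plan's own 43 and f, not the inferred formula or base cost. The squared signal scales with n:

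- √(17.8 × 40 / 43) − 2.576 = 4.069 − 2.576 = 1.493
- Φ(1.493) = 0.932

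Power is about 93% and beta about 0.07, against the stated 95% and 0.05.

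**4. Shortfall in patients.** 43 − 40 = 3 per group; 129 − 120 = 9 in total.

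**5. The 38% scenario (p1 = 1.00, p2 = 0.62).**

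| Method | n per group |
|---|---|
| Unpooled | 17.8 × 0.62 / 0.38 = 29.04 |
| Pooled | 34.4, rounded up to 35 |
| Pooled with continuity correction | 39.4, rounded up to 40 |

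Power at 40 by the unpooled formula: 0.38 / √(0.62 × 0.38 / 40) − 2.576 = 4.951 − 2.576 = 2.375, so about 99%.

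**6. Can one method explain both numbers?** The unpooled formula gives 43 and 29. The pooled formula with continuity correction gives 56 (on the 4841 euro base) and 40. None of the methods tried gives 43 for the 2000 euro difference and 40 for the 38% difference.

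**The case against.** The best defence is that the 38% difference is the trial's real design effect. It is the sponsor's own estimate, it supplies the printed p1 and p2, and the abstract names it. On that view the 2000 euro figure is a check against other countries, and *more conservative* may mean larger than the roughly 29 per group that 38% requires. For 38%, 40 per group meets the stated beta with room to spare by the unpooled formula. This part stands, and it means that the trial as a whole cannot be called undersized. It does not rescue the sentence as printed: 29 appears nowhere, and the *therefore* follows directly on 43.

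A reader might go further and infer that 40 follows from neither scenario, so that the abstract misreports its basis. The documents do not support this. No formula is printed, and a standard pooled calculation with continuity correction gives exactly 40 for the 38% inputs. That may be coincidence, but the abstract may equally be right. For the same reason the abstract should not simply be rewritten to name the 2000 euro difference: that would tie 40 to a scenario for which the plan itself states 43.

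A reader might also object that no margin for loss over the one-year follow-up is given. A condensed article can leave that to the full protocol, so it is not part of this point.

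Finally, it can be said that 93% is itself a weak figure, because mean costs are entered as if they were proportions, with no standard deviation. That is true, and it applies to 43 and 40 alike. It limits what the 93% is worth and is a reason to prefer a proper cost calculation. It does not make 40 larger than 43.

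**Conclusion.** The point holds in a limited form. The text calls a size of 40 conservative immediately after stating a need of 43, and the abstract and methods section give different bases for the same 120. For the 2000 euro scenario the shortfall is 3 per group (9 in total), and power is about 93% rather than 95%. That figure rests on two things: taking the plan's 43 as delivering its stated beta, and the usual scaling of power with n. For the 38% scenario 40 is adequate on the printed inputs.

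The loss is small and nothing in the conduct of the study changes. It is worth correcting because the stated beta is not met for a scenario the plan cites, and the correction is cheap. Which effect the size was really based on cannot be settled from the article; only the sponsor can say.

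**What to change.** 1. In the Sample size calculation section, delete the claim that 40 is more conservative, or say that it is relative to the size needed for the 38% difference and print that size with the formula that gives it.
2. Keep 40 per cohort and state the power it gives for each scenario. For 2000 euro this is about 93% on the plan's own approach. Preferably replace it with a calculation for continuous costs that states the standard deviation assumed. Raising 40 to 43 would not in itself establish the power, for want of that standard deviation.
3. Reconcile the abstract with the methods section so that both name the same effect as the basis of the 120 patients.

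The cost is a wording change in two places and a slightly less favourable stated power for the 2000 euro scenario. A continuous-cost calculation would need an assumed standard deviation, which the article does not give, and its result cannot be predicted from the article. No extra patients are needed.

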#### Economic evaluation

In the cost minimization study direct medical costs and the indirect non medical costs are estimated. For the direct medical costs the method of real cost price calculation will be used. This will include the additional costs of laparoscopy, of ERAS care, as well as the differences due to complications and readmission. For indirect non medical costs the friction cost method will be used [23]. This also allows us to limit the study period to one year post operatively. On the direct non medical costs and indirect medical costs assumptions of equality are made and these costs are not accounted for in this study.

### Data collection and monitoring

Data are collected in a specially designed case-record form, both in the outpatient clinic as during hospital stay. Preoperatively, as well as 6 weeks, 12 weeks and one year postoperatively quality of life questionnaires (SF-36/GIQLI, Vaizey) are filled in by the patient.

The overall study period is 30 months: three cohort periods followed by one year of data analysis and synthesis. Because of the end points used (i.e. direct medical costs and indirect medical costs due to rehabilitation to normal work/activity), a longer follow up is not indicated. At one year all important differences in recovery and rehabilitation to normal life and work can be analyzed. Middle and long term outcomes measures (like oncological recurrences and late secondary complications like adhesions and incisional hernias) will not be included. Histopathological result of resections will be evaluated and compared.

There will be regular contact between the study coordinators and the participating centers, and all included data will be monitored by a research fellow.

## Discussion

Extensive literature exists on ERAS and laparoscopic colon surgery. Regarding the comparison between ERAS recovery and conventional care level 1a evidence exists, showing at least equality and possibly improvement of clinical outcome [18]. Four level 1a reports exist on open versus laparoscopic colon surgery[2,3,12,17]: generally short term results of laparoscopic surgery are better, but no differences on middle and long term clinical outcome are found. Concern has existed on long term oncological outcome, but four level 1b studies (RCT's) have indicated equality in middle and long term (5 years) oncological outcome [4,13,15,16]. One level 1b study indicates that ERAS recovery is as effective in open and laparoscopic surgery, which theoretically biases and diminishes the superiority in short term results of laparoscopic compared to open surgery [6].

Abovementioned studies have convincingly shown that the results of ERAS recovery and/or laparoscopic surgery are at least comparable to those of the conventional surgical approach in colon carcinoma. Long term clinical results as well as surgical-oncological results are equal.

One RCT (level 1b) and three level 2b studies[14,20,24,25] on cost effectiveness of open versus laparoscopic surgery exist. Ignoring possible bias abovementioned, higher operation theatre expenses are leveled down by shorter hospital stays. Only one level 2b cost effectiveness study is available on open conventional recovery versus open ERAS recovery or the combined laparoscopic ERAS programs [26].

No ongoing studies focusing on cost minimization are reported so far. This study seeks to improve the lack of cost minimization data in literature, and may therefore provide important information on the justification of changing treatment policies and investments in hospital facilities for colon surgery.
